**Methodology:** A cross sectional study and a randomized controlled trial will be done. For the survey, random sampling will be used to select 340 children. Hemoglobin, serum ferritin, C- reactive protein and anthropometric measurements will be taken and used as the baseline data for the experimental study. In the randomized controlled trial, 100 children with hemoglobin level of less than 11 mg /dl and above 7 mg/dl (mild and moderate anemia) will be recruited into the trial after informed consent. Severely ill individuals will be referred to Hawassa Referal Hospital. Kebele-stratified simple random sampling will ensure 1:1 allocation to each group. Sequentially numbered, opaque, sealed envelopes will be used to assure concealment of allocation. The study subjects and parents (other caregivers in the absence of parents) will be kept uniformed about the trial allocation. Statistical analysis will be done using the latest SPSS version and ENA for SMART software. The survey will present descriptive statistics including frequencies, means, ranges and demographic characteristics of the population. The trial will be analyzed according to the intention-to-treat principles using logistic crude and site adjusted regression models with a mean difference in Hemoglobin as the primary outcome measure.

**Conclusion:** This research project has the potential to be hypothesis generating and will inform policy makers and scientists about amaranth’s potential to combat malnutrition specifically iron deficiency in the area.

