## 2.2. Hypothesis of this study

**HO:** Feeding 150gm of bread containing 70 mass percentage amaranth grain and 30 mass percentage chickpea per day for mild and moderate anemic children 24.0 up to 59.9 months of age for 6 months will not increase the mean hemoglobin level by 0.7g/dl compared to 150gm of 100 percent Maize containing bread in Tulla sub city southern Ethiopia.

**HA**: Feeding 150gm of bread containing 70 mass percentage amaranth grain and 30 mass percentage chickpea per day for mild and moderate anemic children 24.0 up to 59.9 months of age for 6 month will increase the mean hemoglobin level by 0.7g/dl compared to 150gm of 100 percent maize bread in Tula sub city ,southern Ethiopia.

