## Sample Size

The base line data (survey part) will be used as a basis for the trial part. After completing the survey part the trial sample will be recruited from the survey study participants, in this way the survey will be providing the baseline data for the trial. The survey sample size will be 340 considering a need for 100 trial participants, 33% of mild and moderate anemia prevalence in south Ethiopia, 0.5 degree of precision and 95% confidence intervals. The survey sample size may be increased till the numbers of eligible individuals are identified for the trial if anemia is less prevalent than 33%.

The sample size of the trial is calculated by using Stata I.C. 14 software using the sample size command, considering 0.7 mean difference,1 standard deviation, power 90% and attrition rate 12% the total sample size will be 99 (100) in the two groups. The total sample will be divided in to the amarnth70%/chickpea30% versus the maize 100% groups. Thus it will be 50 in the amaranth/chickpea group and 50 in the maize group ([2](#_ENREF_2)).

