# Study variables

The primary outcome measure of this study will is hemoglobin of children and serum ferritin. The secondary outcomes are anthropometry measures (height/length, weight and mid-upper-arm circumference) (anthropometric z- scores will be derived based on WHO growth standards 2006 (give reference)), conjunctiva pallor and child morbidity pattern including hospitalization, diarrhea, cough and fever (type, frequency, duration and symptoms of illnesses). Potential effect modifiers and confounders will be captured to describe the population and look at the successfulness of randomization (sex, education level, occupation and income), dietary practices (number of meals and frequency of food consumption) including use of amaranth in the diet and type of staple foods.

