# Statistical methods

Data will be entered in to epidata.dk and transferred in to SPSS (version 20.0) software for analysis. ENA for SMART software will be used to convert anthropometric data (weight, height) to z-scores and percent of the median in terms of wasting, underweight and stunting. Data on hemoglobin and serum ferritin levels will be described by using descriptive statistics (mean and percentages) and will be summarized by using tables and figures.

Data on dietary practices, nutritional status, morbidity patterns and serum levels will be described by using descriptive statistics (mean and percentages) and will be summarized by using tables and figures. The descriptive variables will be presented by arm to assess successfulness of the randomization and to describe the study population. Intention to treat analysis using logistic analysis for the main trial outcome hemoglobin will be done and adjustment will only be done for skewed and potentially confounding factors.

Further, descriptive statistics including morbidity prevalence and dietary practices and food diversity will be described from the survey. The relationships between variables such as sex and type of illness which are categorical in nature will be established by using chi-square. Paired t - test will be used to determine if there is a significant difference between the dietary practices (number of meals, diet diversity score), nutritional status, morbidity patterns (frequency and duration of illness), mean hemoglobin level and serum ferritin levels. Simple regression analysis will be used to determine the contribution of dietary practices and morbidity patterns to nutritional status hemoglobin and serum ferretin levels. Multiple regression analysis will be used to determine the extent to which dietary practices and morbidity patterns predict hemoglobin serum ferritin and nutritional status.

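### The primary analysis is named as logistic regression, but the hypothesis and sample size concern a difference in mean hemoglobin

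*Protocol*

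**What the plan says.** Two places in the protocol name the primary analysis, and both choose a logistic model.

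- Statistical methods: "Intention to treat analysis using logistic analysis for the main trial outcome hemoglobin will be done".
- Summary, Methodology: "using logistic crude and site adjusted regression models with a mean difference in Hemoglobin as the primary outcome measure".

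The rest of the design is on the scale of the mean.

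- Hypothesis (2.2): the amaranth bread "will increase the mean hemoglobin level by 0.7g/dl compared to 150gm of 100 percent maize bread".
- Research question 2 (2.1) also asks about a 0.7 increase in mean hemoglobin, and General objective two asks about an increase of 0.7 g/dl.
- Sample Size: "considering 0.7 mean difference,1 standard deviation, power 90% and attrition rate 12% the total sample size will be 99 (100) in the two groups".
- Study variables: "The primary outcome measure of this study will is hemoglobin of children and serum ferritin". No cut-off is attached to hemoglobin as an outcome.

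The value 11 appears in the protocol as part of the survey's definition of iron deficiency anemia and as the upper eligibility limit. It is not given as a trial endpoint.

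**The concern.** Hemoglobin is continuous. Ordinary logistic regression models the probability of a binary event and yields an odds ratio, so it cannot deliver a mean difference in g/dl. The Summary sentence therefore contradicts itself: it pairs a logistic model with a mean difference.

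Two things are at stake if the text is followed literally. First, the analyst must create a binary outcome that the protocol does not define, possibly after seeing the data, and the trial then gives no primary estimate or confidence interval for the 0.7 g/dl question. Second, dichotomising a continuous outcome discards information, so the 90% power in the Sample Size section no longer describes the planned test.

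**Working it through.** **Inputs**

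- Difference 0.7, SD 1, power 90%, attrition 12%, total 99 (100): Sample Size.
- Allocation: "Thus it will be 50 in the amaranth/chickpea group and 50 in the maize group".
- Alpha: not stated for the trial. I assume 0.05 two-sided.
- Cut-off for a binary outcome: none stated. I assume 11, the eligibility limit, for illustration.
- Mean hemoglobin in the maize arm at the end of feeding (m): not stated. I vary it from 9.5 to 12.0.
- Hemoglobin is taken as normal with the protocol's SD of 1 in each arm.

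**Step 1. Reproduce the stated sample size as a comparison of means**

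Normal approximation: n per arm = 2(1.960 + 1.282)² / 0.7² = 42.9, so 43. The t-based calculation gives 43.9, so 44 per arm and 88 in total.

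Attrition: 88 × 1.12 = 98.6, so 99; or 88 / 0.88 = 100. Both match the stated 99 (100). One-sided 0.05 gives only 79 to 82, so the two-sided assumption is the one that fits.

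Power of the two-sample t-test is 90.1% with 44 per arm and 93.4% with 50 per arm. The protocol's own total is thus what a two-sample test of means requires.

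**Step 2. Power if hemoglobin is dichotomised at 11**

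Proportions below the cut are p₁ = Φ(11 − m) in the maize arm and p₂ = Φ(11 − m − 0.7) in the amaranth arm. These go into a two-proportion test with pooled variance under the null.

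Worked case, m = 10.65:

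- p₁ = Φ(0.35) = 0.637, p₂ = Φ(−0.35) = 0.363, difference 0.274, odds ratio 3.07.
- Null SE = √(2 × 0.25 / 44) = 0.1066. Alternative SE = √(2 × 0.637 × 0.363 / 44) = 0.1025.
- Power = Φ((0.274 − 1.96 × 0.1066) / 0.1025) = Φ(0.63) = 73.6%.

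| Maize-arm mean m | p₁ | p₂ | Power, 44 per arm | Power, 50 per arm | n per arm for 90% |
| --- | --- | --- | --- | --- | --- |
| 9.5 | 0.933 | 0.788 | 50.2% | 55.5% | 118 |
| 10.0 | 0.841 | 0.618 | 66.0% | 71.7% | 81 |
| 10.3 | 0.758 | 0.500 | 71.4% | 77.0% | 72 |
| 10.65 | 0.637 | 0.363 | 73.6% | 79.0% | 69 |
| 11.0 | 0.500 | 0.242 | 71.4% | 77.0% | 72 |
| 11.3 | 0.382 | 0.159 | 66.0% | 71.7% | 81 |
| 12.0 | 0.159 | 0.045 | 42.4% | 47.1% | 146 |

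Simulated Wald tests from a logistic model, 44 per arm and 2,000 replicates, agree: 68%, 73% and 66% at m = 10.0, 10.65 and 11.3.

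**Step 3. Does the choice of cut matter?**

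Only the distance between the cut and the arm means enters the formula, so moving the cut is the same as moving m. The best position is midway between the two means, which is the m = 10.65 row. Under these assumptions no cut does better than 73.6% with 44 per arm, or 79.0% if nobody is lost.

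At that best cut, 90% power needs 69 per arm: 138 / 0.88 = 156.8, so 157 in total against the planned 100.

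**Step 4. Does any other stated method fill the gap?**

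Statistical methods also lists a paired t-test that covers mean hemoglobin. A paired test does not compare two independent arms. The simple and multiple regressions there relate dietary practices and morbidity to hemoglobin and do not include trial arm. No stated method estimates the between-arm difference in means.

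**The case against.** The strongest reply is that 'logistic' was written for 'linear'. The Summary names a mean difference in the same sentence, and the hypothesis and sample size are on the mean scale. On that reading nobody intended to dichotomise, power stays at 90%, and the defect is one wrong word in two places. This is plausible, and it makes the power loss conditional. It does not remove the contradiction: both analysis statements name the wrong model for the primary outcome, and an SAP that named a linear model would then depart from the protocol.

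Other points on that side:

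- The cut-off, the final maize-arm mean and alpha are all assumed. This stands, so the exact loss is unknown. That power falls below 90% does not depend on the cut or on the maize-arm mean.
- Study variables also names serum ferritin as primary, and PICO lists change in hemoglobin. So not every statement of the primary outcome is a difference in mean hemoglobin. The hypothesis and the sample size are.
- A logistic model with arm regressed on continuous hemoglobin would keep about 91% power in simulation. The protocol does not describe such a model, and it would still give no difference in g/dl.

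**Conclusion.** The concern holds. The model named for the primary analysis cannot estimate the effect on which the trial is hypothesised and sized, and no other method in the protocol does so between arms. This conclusion follows from the text alone and needs no assumption.

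The power figures apply only if the text is followed literally and hemoglobin is dichotomised. With normal data, SD 1, two-sided alpha 0.05 and 44 completers per arm, the chance of missing a true 0.7 g/dl difference rises from about 10% to at least 26%, and to 58% at a final maize-arm mean of 12.0. Because the sentence governs the primary analysis, it has to be corrected even if it is only a slip.

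**What to change.** In the Summary (Methodology) and in Statistical methods, replace logistic by linear regression of hemoglobin at the end of feeding on trial arm, by intention to treat. Report the mean difference in g/dl with its 95% confidence interval as the primary result.

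- Keep the crude and site-adjusted models that the Summary already plans, with kebele as the adjustment because randomization is stratified by it, and say which of the two is primary.
- State whether the outcome is the end value or the change, since PICO lists change. With baseline hemoglobin as a covariate, both give the same arm effect.
- Remove mean hemoglobin from the paired t-test sentence in Statistical methods, or restrict that test to within-arm description.
- If a binary result such as hemoglobin still below 11 is wanted, define it with its cut-off as a secondary outcome and use logistic regression for that outcome only.

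The cost is a change of wording in the Summary and Statistical methods, plus an entry in Study variables if a binary secondary outcome is added. No new data are needed, and the total of 100 stands.

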**Specific objective**

1. To compare the hemoglobin values in children receiving amaranth grain containing bread and children receiving maize bread in Tulla sub city South Ethiopia.
2. To compare the ferritin values in children receiving amaranth grain containing bread with children receiving maize bread in Tulla sub city south Ethiopia.
3. To compare the anthropometry indices in children receiving amaranth grain containing bread with children receiving maize bread in Tulla sub city south Ethiopia.
4. To compare incidence of childhood illness in children receiving amaranth grain containing bread with children maize bread in Tulla sub city south Ethiopia.
5. To compare cost effectiveness of amaranth containing bread on the prevention of iron deficiency anemia in Tulla sub city south Ethiopia
6. To compare compliance and adherence of mother between amaranth containing bread and maize bread groups.

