## Sampling Technique

All children age 24.0-54.0 months will be registered in the selected Kebelles. From the registered children 340 children will be select by using simple random selection for survey part.

After assessing Hgb, 100 children with mild and moderate anemia status will be included in the trial. The included children will be allocated randomly 1:1 to amaranth70% chickpea30% versus maize100% 150g daily bread. Single randomization stratified by Kebelle will be used.

Randomization will be done using random org sequence free soft ware. Researchers not involved in the field work in Hawassa University will provide the sequence; researchers at the partner institution UiB will provide the seed number.

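### The paired t-test named for ferritin, anthropometry and other outcomes has no defined pair and cannot answer the between-arm objectives; for hemoglobin, regression to the mean also makes a false within-arm rise likely

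*Protocol*

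**What the plan says.** The third paragraph of Statistical methods begins with the survey ("dietary practices and food diversity will be described from the survey"), moves to a chi-square test for categorical variables, and then states "Paired t - test will be used to determine if there is a significant difference between the dietary practices". The list in that sentence goes on to nutritional status, morbidity patterns, and "mean hemoglobin level and serum ferritin levels". The two measurements that form a pair are not named.

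The paragraph before it gives the trial's main outcome its own analysis: "Intention to treat analysis using logistic analysis for the main trial outcome hemoglobin will be done". The Summary likewise describes crude and site-adjusted logistic regression, with a mean difference in hemoglobin as the primary measure.

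The specific objectives under General objective two compare arms: "To compare the hemoglobin values in children receiving amaranth grain containing bread and children receiving maize bread" and "To compare the ferritin values in children receiving amaranth grain containing bread with children receiving maize bread", with parallel objectives for anthropometry and childhood illness. Study variables lists serum ferritin as primary together with hemoglobin.

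On design, Sampling Technique says "The included children will be allocated randomly 1:1", with stratification by kebelle. Entry requires a survey hemoglobin of 7 to below 11, and Sample Size says of the survey that "in this way the survey will be providing the baseline data for the trial".

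**The concern.** A paired t-test needs two measurements that belong together. The cross-sectional survey gives one measurement per child. The arms hold different children, randomised individually and not matched. The only usable pairs are repeated measurements of the same child during the trial, so an analyst who follows the text literally would test before against after within each arm.

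That test asks whether an arm changed, not whether the arms differ. Anything that moves both arms enters it: deworming, which the Trial Schedule plans twice without distinction by arm; the monthly health education; and the energy and iron that both breads supply. For hemoglobin, selecting children on a low value and using the same value as baseline adds regression to the mean.

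The risk is that a significant change in the amaranth arm, particularly beside a non-significant one in the maize arm, is taken as evidence of benefit.

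**Working it through.** **1. The design implied by the plan's own sample size.** Inputs from Sample Size: difference 0.7, SD 1, power 90%, attrition 12%. Two-sided alpha of 0.05 is assumed, as none is stated.
- Normal approximation: n per arm = 2 × (1.960 + 1.282)² × 1² / 0.7² = 42.9, so 43.
- t-based solution: 43.87, so 44 per arm and 88 in total.
- Attrition: 88 × 1.12 = 98.6, which gives the stated 99; 88 / 0.88 = 100 gives the rounded total.

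The plan's figure is reproduced as a comparison of two independent groups, not of pairs.

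**2. Which pairs exist.**

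| Comparison | Pairs? | Answers the trial objectives? |
|---|---|---|
| Survey, cross-sectional | No | No |
| Amaranth against maize | No; independent groups, stratified by kebelle | Yes, with an independent-groups method |
| Before against after in one arm | Yes; Trial Schedule repeats hemoglobin, ferritin and anthropometry | No |

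**3. Which tests Statistical methods names.** Hemoglobin has the intention-to-treat analysis. The chi-square test is for categorical variables. The simple and multiple regressions use dietary practices and morbidity as predictors, not trial arm. That leaves the paired t-test as the only named test of difference for ferritin and anthropometry.

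**4. Hemoglobin with no true change.** Inputs: 33% below 11 (Sample Size); entry at 7 to below 11 (Inclusion criteria); 44 analysed per arm (step 1). Three inputs are assumed: the protocol's SD of 1 applies to the survey population, values are normal, and the baseline-to-endpoint correlation r lies between 0.5 and 0.95. Hemoglobin is in g/dl, the unit used in the hypotheses.
- Population mean = 11 + 0.44 × 1 = 11.44. The lower limit of 7 is then 4.44 SD below the mean and has no practical effect.
- Children below the 33% point lie on average φ(0.44)/0.33 = 1.097 SD below the population mean, so their baseline mean is 11.44 − 1.10 = 10.34.
- Expected rise with no effect = (1 − r) × 1.097 × SD.
- The chance of a significant rise comes from simulating the paired t-test at n = 44; the nominal value in that direction is 2.5%.

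| r | Null rise (g/dl) | SD of change | Chance of a significant rise in one arm |
|---|---|---|---|
| 0.5 | 0.55 | 0.91 | 98% |
| 0.6 | 0.44 | 0.83 | 93% |
| 0.7 | 0.33 | 0.73 | 84% |
| 0.8 | 0.22 | 0.61 | 65% |
| 0.9 | 0.11 | 0.44 | 37% |
| 0.95 | 0.05 | 0.31 | 20% |

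Over r = 0.5 to 0.9 the artefact is 0.55/0.7 = 79% down to 0.11/0.7 = 16% of the target difference. With SD 0.8 the rise is 0.44 to 0.09, and with SD 1.3 it is 0.71 to 0.14; the chances barely change. The chance that exactly one arm is significant is 2p(1 − p): 2 × 0.646 × 0.354 = 46% at r = 0.8 and 2 × 0.367 × 0.633 = 46% at r = 0.9.

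**5. Ferritin and z-scores.** Children are not selected on low values of these, so the artefact arises only through correlation c with hemoglobin. Drift = (1 − r) × c × 1.097 SD. With c assumed at 0.1 to 0.3 and r at 0.5 to 0.9, drift is 0.01 to 0.17 SD and the chance of a significant rise is about 4% to 19%.

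**The case against.** The strongest reply is that the paired t-test is not the trial's efficacy analysis. Hemoglobin has an intention-to-treat analysis of its own, the hypotheses compare arms, and the paired-test sentence sits in a paragraph that opens with the survey and never mentions bread or allocation. This stands for hemoglobin: a reader might infer that the primary hypothesis rests on a paired test, and the protocol does not say so. The reply is weaker than it looks, because a logistic model does not estimate a mean difference. It also does not extend to ferritin and anthropometry. The Summary could be read as applying the regression models to all trial outcomes, but it names only hemoglobin.

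A second reply is that within-child pairs do exist and a paired t-test is a standard test of change. True, but such a test would be valid for a question that the specific objectives do not ask.

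A third is that the correlation driving the hemoglobin figures is not in the protocol. That also stands. A reader might infer that a false improvement is certain; at r = 0.95 the chance is 20%. Nor may the mechanism be carried over to ferritin or nutritional status. Ferritin is not an entry criterion, and excluding children below −3 Z would, if anything, pull nutritional status the other way.

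Finally, an unseen statistical analysis plan may supply between-arm models. It would still have to override a test that this protocol names.

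**Conclusion.** The concern holds as a wrongly stated test. No pairing available in this study lets a paired t-test compare the arms, yet for ferritin (a listed primary outcome) and anthropometry it is the only test of difference that Statistical methods names. For these outcomes the defect is that the test does not compare arms and is open to changes common to both.

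For hemoglobin alone, regression to the mean adds a likely false within-arm improvement: about 0.55 to 0.11 g/dl, significant in about 98% to 37% of single-arm tests. This rests on SD 1 in the survey population, normality, no time trend, 44 analysed per arm and an assumed correlation of 0.5 to 0.9. The direction follows from the design; the size depends on that correlation.

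The documents do not support the inference that the paired test is the sole test of the main hypothesis, or that the sample size is affected.

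**What to change.** Remove the paired t-test as a test of effect. For hemoglobin, ferritin and anthropometric z-scores, state that arms are compared by intention to treat with a linear model containing arm, the baseline value of the outcome and kebelle. State that illness is also compared between arms; the form of that model, and any transformation of ferritin, can be left to the statistical analysis plan. Report within-child change by arm descriptively, without p-values, and note that baseline hemoglobin is the screening value. If any paired test is kept, name the two time points and label it as within-child change.

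The cost is wording only. The measurements are already scheduled, and 44 analysed per arm still gives about 90% power (0.901, t-based), so the total of 100 stands.
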